## Design

The trial is a 2 × 2 factorial single-blind RCT (Figure 1): the 4 arms of the trial are CSP alone, RYCT alone, CSP and RYCT combined, and treatment as usual (TAU). To ensure enough participants to run viable RYCT groups, we randomise between TAU, RYCT, CSP and combined in the proportions 1:2:1:2. We collect data at baseline (post-consent, pre-randomisation), and 5 and 12 months after the first randomisation, with the main endpoint at 12 months. After randomisation, all participants are free to continue to receive treatment as usual from statutory and voluntary services in their locality. We conducted a feasibility study before the full RCT in accordance with MRC guidance on complex interventions guidance [21].

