#### Cost estimation

The economic evaluation will use responses on the validated CSRI [48] completed with the carer. We will attach nationally relevant unit costs to services used by participants, using the most recent Personal Social Services Research Unit 'Unit Costs' volume where available [52], and costed locally where not, for example for CSP and RYCT. The time inputs of carers and their lost productivity (from giving up or reducing employment) will be costed using a range of methods to reflect the opportunity costs to those individuals, and the consequences of differences explored in sensitivity analyses. The primary economic analysis will include costs, both of service use and of carer inputs (a societal perspective).

We shall compare the outcomes and costs of the four allocated groups. For example, we shall interpret CSP as more cost-effective than TAU (both alone or both in combination with RYCT) if: (i) it is both less costly and more effective on the MCS-12; or (ii) it is both more costly and more effective, and the decision maker values the improvement in outcome at more than the additional cost; or (iii) it is both less costly and less effective and the decision-maker attaches lower value to the loss of outcome than the cost savings. In the fourth option, when CSP is more costly and less effective than TAU, the decision maker-would prefer TAU.

To quantify options (ii) and (iii) in this example, we shall estimate the ICER, namely the mean cost difference between CSP and TAU (both alone or both in combination with RYCT) over the follow-up period of 12 months divided by the mean difference between these groups in the MCS-12 over those 12 months. We will also estimate net benefit (NB) for each dyad from the standard formula:

NB=λ×E-C

where:

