E is effectiveness, namely the change in the primary outcome; C is the cost for that dyad (services used by the carer and the person with dementia, plus indirect costs of carer time); and λ is the decision-maker's willingness to pay for one additional unit of outcome. After calculating net benefits for each dyad for plausible values of λ, we shall address the expected skewness in the distribution of NBs by 'bootstrapping'; this is the technique of drawing (say) 10,000 independent replicates with replacement from the original sample of (say) 240 dyads while keeping the four allocated groups at their original sizes. For each value of λ we shall use these replicated samples to estimate the true proportion of dyads whose net benefit is positive, and derive a CEAC plotting the likelihood of CSP being cost-effective relative to TAU (both alone or both in combination with RYCT) against λ, the decision-maker's willingness to pay. We shall conduct sensitivity analyses to explore the effect on conclusions of varying key assumptions about costs and outcomes.

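### The acceptability curve is built from the share of dyads with positive net benefit, which is not the probability that CSP (or RYCT) is cost-effective

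*Protocol article*

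**What the plan says.** The net-benefit procedure is in the protocol article under Cost estimation and runs in four steps.

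- Net benefit is a quantity per dyad: "We will also estimate net benefit (NB) for each dyad from the standard formula", namely λ times E minus C.
- Both terms belong to that dyad alone: "E is effectiveness, namely the change in the primary outcome", and "C is the cost for that dyad (services used by the carer and the person with dementia, plus indirect costs of carer time").
- The bootstrap resamples dyads within arms: "drawing (say) 10,000 independent replicates with replacement from the original sample of (say) 240 dyads while keeping the four allocated groups at their original sizes".
- At every λ the plan will "use these replicated samples to estimate the true proportion of dyads whose net benefit is positive", and then "derive a CEAC plotting the likelihood of CSP being cost-effective relative to TAU".

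The ICER in the same section is set up differently. Its numerator is "the mean cost difference between CSP and TAU (both alone or both in combination with RYCT) over the follow-up period of 12 months", a contrast of group means, and its denominator is the matching contrast in MCS-12.

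The procedure is written out for CSP as an example. The section Cost-effectiveness analysis gives RYCT, and CSP and RYCT combined, the same five stages. The section Secondary cost-effectiveness analyses repeats the primary analyses from a health and social care perspective and says that the QALY analyses follow the same stages exactly.

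**The concern.** A CEAC answers a question about two groups: given the data, how likely is it that one programme has the higher mean net benefit at a given λ? The stated calculation contains no second group. It counts dyads for which λ times the carer's own improvement exceeds everything spent on that dyad, including care that has nothing to do with CSP. Two consequences follow.

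- Costs common to all arms cancel in a comparison between groups, but they drive the count of dyads. Expensive background care pulls the written curve down for every arm.
- Bootstrapping a proportion of dyads returns the sample proportion with its sampling error. It does not turn that proportion into a probability about a difference in means.

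An analyst who follows the text would label as the likelihood of cost-effectiveness a number that is something else. The same error would carry into all three primary economic comparisons and the secondary ones, in a trial whose stated aims include cost-effectiveness. A programme that is good value could appear to have a low chance of being so.

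**Working it through.** The document gives no CEAC figure to reproduce. The check is whether the written quantity and the CEAC can agree.

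**1. λ = 0.** Here NB = 0 × E − C = −C for every dyad. If every dyad has a positive cost, the share with NB > 0 is 0%. The CEAC at λ = 0 is the probability that mean cost is lower with CSP, which can be anything from 0 to 100%. Decision rule (i) in the same section counts CSP as more cost-effective when it is cheaper and more effective, whatever λ is. The written curve would show 0% at λ = 0 in exactly that case. This step needs no assumed figure.

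**2. Very large λ.** Costs become negligible.
- As written, the share tends to the proportion of carers who improve. Assume a correlation of 0.5 between baseline and 12 months, so that the SD of change equals the SD of the score, and no drift without CSP. The share is then Φ(0.42) = 66% with CSP and Φ(0) = 50% without.
- The CEAC, if the observed effect equals the planned 0.42 SD, tends to Φ(0.42 / √(2/120)) = Φ(3.25) = 99.9%.

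**3. In between.**

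Inputs from the document: 240 completed dyads and an effect of 0.42 SD for CSP (Sample size); "we randomise between TAU, RYCT, CSP and combined in the proportions 1:2:1:2" (Design), which gives 40, 80, 40 and 80 dyads, hence 120 with CSP and 120 without.

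Assumptions not in the document: SD of MCS-12 change 10 points, so the effect is 4.2 points; gamma-distributed dyad costs with SD 75% of the mean; mean cost without CSP of 20,000 (SD 15,000) or 5,000 (SD 3,750); CSP adds 500; costs and outcomes independent.

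Formulas:
- As written: share = P(λE − C > 0) over CSP dyads, that is, the average over C of Φ((4.2λ − C) / (10λ)).
- CEAC: Φ((4.2λ − 500) / √[(2/120)(100λ² + SD_C²)]).

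Example at λ = 1,000 with mean cost 20,000: numerator 4,200 − 500 = 3,700; denominator √[(2/120)(100,000,000 + 225,000,000)] = 2,327; Φ(1.59) = 94%.

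| λ per MCS-12 point | Mean 20,000: as written | Mean 20,000: CEAC | Mean 5,000: as written | Mean 5,000: CEAC |
|---|---|---|---|---|
| 0 | 0% | 40% | 0% | 15% |
| 500 | 7% | 78% | 30% | 98% |
| 1,000 | 17% | 94% | 46% | 99.6% |
| 2,000 | 32% | 99% | 56% | 99.9% |
| 5,000 | 51% | 99.9% | 62% | 99.9% |

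**4. Simulation with the plan's bootstrap.** One simulated data set per scenario (240 dyads in arms of 40, 80, 40 and 80; slightly wider gamma costs, shape 1.5; 4,000 stratified replicates; CSP contrast averaged over the two RYCT strata) gave the same picture.

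- Mean cost 20,000, λ = 1,000: 18% as written against 93%. The bootstrap average of the written quantity was 0.184 and the plain sample proportion 0.183, so resampling added nothing.
- Mean cost 5,000, λ = 1,000: 43% as written against 99.5%.
- CSP 3,000 cheaper and 4.2 points better, λ = 0: 0% as written against 95%.
- Group means set equal on cost and effect: as written, the share for CSP dyads rose from 0% at λ = 0 to 33% at λ = 5,000, while the CEAC stayed at about 50% throughout.

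**The case against.** The strongest reply is that this is a slip of wording and not a planned method. The curve's stated axis is comparative and conventional. The decision rules and the ICER are contrasts between groups, and holding the four arms at their original sizes in each replicate only makes sense if arms are to be compared. On that reading, dyads was written where replicates with positive incremental net benefit were meant. Net benefit per dyad is also a legitimate input to a comparison of means, so the formula itself is not at fault. Finally, the ICER is correctly specified, no threshold on the curve is set as a decision rule, and the illustrative percentages depend on costs the document does not give.

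Much of this stands. The intention was probably right, the formula and the stratified bootstrap can stay, and the in-between percentages are illustrations: at λ = 1,000 the written share moves from 17% to 46% when the assumed mean cost falls from 20,000 to 5,000. The text also does not say whether the share is taken over CSP dyads, all dyads, or each arm in turn. None of this rescues the sentence. It names dyads, follows a net benefit expressly defined per dyad, and is the only operational route given from replicates to curve. Whichever dyads are counted, the result is not a probability about a mean difference. Condensing a fuller document can explain a missing detail, but here a rule is stated and it is the wrong one.

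**Conclusion.** The concern holds. As written, the step from bootstrap to CEAC estimates the wrong quantity and conflicts with the protocol's own decision rule (i). At λ = 0 the written curve is 0% whatever the comparison between groups shows, provided only that every dyad has a positive cost. At large λ it tends to the share of carers who improve (66% with CSP under the stated assumptions), where the CEAC would approach 99.9% if the observed effect is 0.42 SD. In the illustrations, at λ = 1,000 per point the gap is 17% against 94% or 46% against 99.6%, depending on the assumed mean cost. The sizes rest on those assumptions; the mismatch does not.

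The error covers the CEAC for CSP and, through the shared stages, those for RYCT, the combined comparison, the health and social care perspective and the QALY analyses. The ICER, the effectiveness analyses and the sample size are not touched. It must be corrected before the economic analysis is run.

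**What to change.** Replace the clause on the proportion of dyads with wording such as: *For each λ and each bootstrap replicate, calculate the difference in mean net benefit between the compared groups (CSP versus no CSP, stratified by RYCT; RYCT versus no RYCT, stratified by CSP; combined versus TAU). The CEAC at that λ is the proportion of replicates in which this difference exceeds zero.* State that the same definition applies to the secondary perspective and to the QALY analyses.

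The cost is two or three sentences. Net benefit per dyad, the 10,000 replicates and the resampling within arms are kept, and no new data are needed.

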#### Secondary cost-effectiveness analyses

A number of secondary economic analyses will be conducted.

The cost-effectiveness analyses set out above (primary analyses) will be repeated from a health and social care system perspective, which in this case will mean looking only at costs to the health and social care system, but still focusing on MCS-12 as the outcome measure.

We will use the EQ-5D for carers to calculate utility using societal preference weights, and examine cost-effectiveness with outcomes measured as utility (quality-adjusted life years), first from a societal perspective and then from a health and social care system perspective. The stages of analysis will match exactly the approach to be adopted for the primary cost-effectiveness analyses described above. The results from these analyses will be in the form of cost per additional quality-adjusted life year (QALY) and will permit comparison with studies in other clinical fields and with (for example) NICE recommendations.

Other outcomes (for carers and people with dementia) will be examined alongside costs in a series of cost-consequences analyses to cast further light on the impact of the interventions.

## Discussion

The design of the trial is unusual since there are few psychosocial intervention studies that merit a factorial design; compare individual, group, and combined interventions; and undertake a cost-effectiveness analyses, particularly where the unit of consideration is the dyad rather than the carer. We know of no examples of factorial studies that assess the impact of interventions on the mental health of family carers. Hence this pragmatic trial has the potential to inform and potentially influence policy and practice not only in relation to care and treatment for dementia, but also in other chronic mental and even physical illnesses. The SHIELD CSP-RYCT trial aims to evaluate peer support focused on both the carer through CSP and dyad through RYCT. This combination seeks to support the family carers, their relatives with dementia, and the relationship they share. Supported carers have the potential to care for the person with dementia to provide them with a better quality of life than those in residential care [2] coupled with economic advantages.
